#### Analysis of the relation between exposures and outcomes

3.6.2

In all analyses, the researchers will blind the identity of the comparison groups. Statistical analysis will be performed using multilevel mixed-effects linear and nonlinear models in R Studio and Python (56). These models offer several advantages over standard parametric and non-parametric tests: they are more robust to violations of normality, which is common in biological data, and they do not require homoscedasticity (57, 58). Additionally, they accommodate the nested structure of our data (trials nested within sessions, sessions nested within participants, participants nested within groups) and handle missing data more effectively than repeated-measures ANOVA. Normality of residuals will be assessed visually with quantile-quantile (Q-Q) plots and statistically using the Shapiro–Wilk test; homoscedasticity will be evaluated with the Breusch–Pagan test (59, 60). Data will be considered statistically significant at a p-value < 0.05. Given the large number of variables related to diet, nutritional status, ASD severity, and sensorimotor integration, exploratory analyses will include the Kruskal–Wallis test to compare groups on non-normally distributed variables (61). In addition, cluster analysis (k-means clustering and equivalent algorithms) will be used to identify profiles of gut microbiota or dietary patterns (62).

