**Methods:**

This comparative cross-sectional study will recruit 100 autistic children and adolescents (aged 3–17 years) and 200 age-/sex-matched NA peers (including 100 with developmental disorders other than autism). Autism severity will be assessed using the Childhood Autism Rating Scale; NA peers will be screened with the Autism Spectrum Quotient-10. Dietary intake will be evaluated via three 24-hour dietary recalls, supplemented by questionnaires on socioeconomic status, health, and medications. Nutritional status (anthropometry, bioimpedance) and gut microbiota composition and diversity will be assessed. SMD proxies (sensory gating, sensory adaptation) will be measured using a smartphone application.

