#### Sample size

2.2.4

The sample size was determined based on the expected difference in malnutrition prevalence between autistic children and their NA peers in a cross-sectional comparison. According to the *Encuesta Nacional de Salud y Nutrición* (24), 35% of the Ecuadorian children younger than 11 years of age are overweight or obese, while among adolescents the prevalence of overweight or obesity is 30%. The prevalence of extreme thinness is 2% among Ecuadorian children and adolescents. Based on these figures, we assumed an approximate malnutrition prevalence of 37% in the NA population.

There is no published data on prevalence of malnutrition in Ecuadorian autistic children up to date. To estimate this value, we referred to data from a recent study in another Latin American country (Mexico), which reported a malnutrition prevalence of 57.50% among autistic children (45% obese/overweight, and 12.50% underweight) (25). To estimate the sample size required to detect this difference (~20.50%) between the groups, we used the formula for comparing two independent proportions in a two-sided hypothesis test (26):

$n=\frac{{\left(Z_{\alpha /2}+Z_{\beta }\right)}^{2}\times [p_{1}(1-p_{1})+p_{2}(1-p_{2})]}{{\left(p_{1}-p_{2}\right)}^{2}}$, where:

$Z_{\alpha /2}$ = 1.96 (corresponding to a 95% confidence level),

$Z_{\beta }$ = 0.84 (corresponding to 80% power),

$p_{1}$ = 0.57 (estimated malnutrition prevalence in autistic children - Group A),

$p_{2}$ = 0.37 (estimated malnutrition prevalence in NA children - Group B).

The formula yields an approximate sample size of 94 participants per group. To account for a projected non-response rate of 5%, the sample size increases to 100 participants per group. This sample size is also adequate for detecting large effect sizes in secondary comparisons, such as the prevalence of SMD, which has been reported to be between 81.50% and 95.00% among autistic children and may reach 16.50% in children of the population (7, 18, 27). Thus, our sample will be sufficient for the validation of the neurometric test, achieving a statistical power close to 1.

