##### Prepulse inhibition of acoustic startle response

3.5.4.1

PPI is the behavioral phenomenon whereby the magnitude of the startle response is inhibited when a short, loud startling sound (the pulse) is preceded by a weaker sound that does not itself elicit a startle reflex (the prepulse). The PPI training session will last approximately 12 minutes, contain 44 trials, and will be administered to all children. We will use a pulse consisting of a 105 dB, 50 ms white noise burst. The prepulse will consist of a 50 ms white noise burst of varying amplitude that is always softer than the pulse, delivered at three different intensities: 10% (soft), 25% (medium), and 40% (high) of the pulse amplitude. For the soft and high prepulse intensities, a fixed interstimulus interval (ISI) of 120 ms will be used between the prepulse and the pulse. For the medium prepulse intensity, ISIs of 60, 120, and 240 ms will be used. The session will begin with 2 practice trials containing white noise bursts at various soft intensities to allow the participant to relax and settle into the movie. Subsequently, 7 blocks of 6 trials will be presented. Each block will consist of one pulse-only trial and five prepulse-pulse trials. The order of trials will be randomized and will differ between blocks. The intertrial interval will be randomly set between 4 and 14 seconds.

*Dependent variables*

Acoustic startle response (ASR) amplitude and variability: The normalized peak eyelid closure amplitude in response to the pulse-alone trials and its standard deviation.ASR latency to peak: The time from pulse onset to the peak of the eyeblink response.Prepulse-elicited response amplitude: The normalized peak eyelid closure amplitude in response to the prepulse-alone.Prepulse-elicited response latency: The time from prepulse onset to the peak of the eyeblink response it elicits.Prepulse-pulse response amplitude and variability: The normalized peak eyelid closure amplitude in response to the pulse when it is preceded by a prepulse, and its standard deviation.Percent PPI: The percentage inhibition of the ASR amplitude due to the prepulse, calculated as: % PPI = 100 - [(mean ASR amplitude on prepulse-pulse trials)/(mean ASR amplitude on pulse-alone trials) × 100].Prepulse excitation: A measure of hyper-responsiveness to the prepulse itself.Habituation: The change in normalized ASR amplitude to pulse-alone trials over the course of the entire session.

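### The stated ground for the mixed models, that they need no equal variances, is wrong for the standard linear model; no variance structure or robust standard error is named in its place

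*Protocol article*

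**What the plan says.** Section 3.6.2 names the model class: "Statistical analysis will be performed using multilevel mixed-effects linear and nonlinear models in R Studio and Python". Among the advantages claimed over standard parametric and non-parametric tests is that "they are more robust to violations of normality, which is common in biological data, and they do not require homoscedasticity". Two sentences later the same section adds that "homoscedasticity will be evaluated with the Breusch–Pagan test", without saying what follows if the test rejects. The significance rule is "Data will be considered statistically significant at a p-value < 0.05".

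No heterogeneous-variance structure or robust standard error is mentioned. Section 4.2 promises sensitivity analyses under other modelling assumptions, in general terms and without naming variance.

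The Abstract sets the group sizes as "100 autistic children and adolescents (aged 3–17 years) and 200 age-/sex-matched NA peers", the latter made up of 100 in Group B and 100 in Group C. Section 2.2.1 allows up to 150 autistic children. No SD is given for any outcome.

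**The concern.** A default linear mixed model estimates a single residual variance and a single between-child variance and builds the standard error of every group contrast from them. It tolerates unequal spread only when group-specific variances are fitted or robust standard errors are used. The sentence therefore credits the model class with a property that depends on an option the text does not select. Having declared the assumption unnecessary, the section then tests it, and read literally a failed test changes nothing.

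The stake is the error rate of group contrasts on continuous outcomes: nutrient intakes, z-scores, Shannon diversity and startle measures. Where one group is both smaller and more variable, a common-variance test rejects too often. A contrast between two groups that are both less variable than the third gets a standard error that is too large, and loses power.

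**Working it through.** **The plan's own figure.** Section 2.2.4 states that "we used the formula for comparing two independent proportions in a two-sided hypothesis test". With 1.96 and 0.84 ("corresponding to 80% power"), p1 = 0.57 and p2 = 0.37:

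n = (1.96 + 0.84)² × (0.57×0.43 + 0.37×0.63) / 0.20² = 7.84 × (0.2451 + 0.2331) / 0.04 = 93.7, so 94 per group, as stated. Then 94/0.95 gives 99, against the stated 100. The figure reproduces. The implied variance ratio for this outcome is 0.2451/0.2331 = 1.05.

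**Inputs for the variance check.** From the documents: nA = 100, nB = nC = 100, alpha 5%, taken as two-sided as in section 2.2.4. Assumed: the SD of child-level values is 1 in Groups B and C and r in Group A. The documents give no value for r, so it is varied. With equal numbers of trials per child, a random-intercept model's test of a group contrast is equivalent to a common-variance test on child means, so child-level formulas apply.

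**Formula.** True size = 2 × [1 − Φ(1.96 × √(V_assumed / V_true))].

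*Autistic versus all non-autistic (100 versus 200).* V_true = r²/100 + 1/200. V_assumed = [(99r² + 199)/298] × (1/100 + 1/200).
- r = 1.5: V_true = 0.0275; V_assumed = 1.415 × 0.015 = 0.0212; 1.96 × √0.772 = 1.722; size 8.5%.
- r = 2: V_true = 0.045; V_assumed = 1.997 × 0.015 = 0.0299; 1.96 × √0.666 = 1.599; size 11.0%.

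*Three-group model, common variance (r² + 2)/3.*
- A versus B, or A versus C: V_true = (r² + 1)/100; V_assumed = 0.02 × (r² + 2)/3.
- B versus C: V_true = 0.02, so the standard error is multiplied by √((r² + 2)/3). For an effect with nominal 80% power, power = Φ(2.80 − 1.96 × √((r² + 2)/3)). At r = 1.5 the factor is √(4.25/3) = 1.19, giving Φ(2.80 − 2.33) = 68%.

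| r | A vs B+C, size | A vs B or A vs C, size | B vs C, size | B vs C, power |
|---|---|---|---|---|
| 0.75 | 3.1% | 4.0% | 7.0% | 84% |
| 1 | 5.0% | 5.0% | 5.0% | 80% |
| 1.25 | 6.9% | 5.9% | 3.3% | 75% |
| 1.5 | 8.5% | 6.7% | 2.0% | 68% |
| 1.75 | 9.9% | 7.4% | 1.1% | 60% |
| 2 | 11.0% | 8.0% | 0.6% | 51% |

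**150 autistic children.** At r = 1.5, V_true = 2.25/150 + 1/200 = 0.0200 and V_assumed = 1.535 × 0.01167 = 0.0179, giving 6.4%. At r = 2 the size is 7.2%.

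**Balanced two-group test.** With 100 versus 100 and only those two groups in the model, V_assumed equals V_true and the size stays at 5.0% for every r.

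**Simulation.** With 10,000 data sets per setting, the common-variance test of A versus B+C had size 7.0%, 8.5% and 11.0% at r = 1.25, 1.5 and 2. Separate variances (Welch) gave 5.0%, 4.7% and 5.2%. A random-intercept mixed model at r = 2 gave 8.7% over 300 fits (Monte Carlo standard error about 1.6 points). This is compatible with the closed form, but too few fits to pin it down.

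**The case against.** Several points against this stand, and they set its limits.

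- **The size is conditional.** A reader might infer that the false-positive rate roughly doubles. That needs an SD ratio of about 1.75 to 2, and the documents give no SD. Below 1 the directions reverse: A versus non-autistic becomes conservative and B versus C liberal.
- **The protocol does not predict larger between-child spread.** A reader might infer that it does, because the Introduction mentions hyper- and hypo-reactivity, section 3.5.4.1 makes "The normalized peak eyelid closure amplitude in response to the pulse-alone trials and its standard deviation" a dependent variable, and section 3.5.4.3 lists baseline eyelid variability among behaviours that differ between groups. The first is background, the second is not said to differ by group, and the third is within-child variation. None bears on diet, anthropometry or alpha-diversity.
- **The 100-versus-200 contrast is not named as primary.** Objectives 1 to 3 are worded as autistic versus non-autistic, but the study is sized on A versus B for binary malnutrition. There the spread is fixed by the prevalence, the ratio is 1.05 even under the planning alternative, and a 1:1 comparison is protected.
- **B versus C contains no autism effect.** Both groups are non-autistic, so its power loss does not bear on autism specificity. A versus C does, with the milder 5.9% to 8.0%.
- **Not every analysis is touched.** Nonlinear models, Kruskal–Wallis, Wilcoxon and PERMANOVA are also planned.

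It can also be said that the variance structure and the use made of Breusch–Pagan are details for an analysis plan. As omissions they would be. The point here is an incorrect statement in the text, which would steer an analyst away from the safeguard. The general promise of sensitivity analyses does not correct it.

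**Conclusion.** The point holds as a correction to section 3.6.2. The statement about homoscedasticity is wrong for the standard linear mixed model, and nothing named in the text makes it true.

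If the autistic group is the more variable by a factor of 1.25 to 2, continuous-outcome tests of 100 versus 200 run at about 7% to 11% instead of 5%. A versus B or A versus C in a three-group model runs at about 6% to 8%, and B versus C becomes conservative and loses power. These figures assume equal SDs in B and C and a common-variance fit. They shrink with 150 autistic children and change direction if autistic children are the less variable. The documents do not support saying that the error rate is doubled, that the comparison the study was sized for is compromised, or that all group contrasts are invalid.

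**What to change.** Delete the statement in section 3.6.2, or qualify it to say that mixed models can accommodate unequal variances when these are modelled.

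For group contrasts on continuous outcomes, make one of these the default:
- group-specific residual and between-child variances (for outcomes measured once per child, a group-specific residual variance is enough); or
- small-sample-corrected cluster-robust standard errors by child.

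Apply the choice regardless of the Breusch–Pagan result, and describe that test as a diagnostic only.

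The cost is a sentence of text and one extra model term. The downside is slightly wider intervals if the variances are in fact equal.

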### Recruitment and patient involvement

2.3

This study protocol was designed in collaboration with a special education school in Quito and a child neurodevelopment center in Riobamba. Both are private centers where autistic children and adolescents receive rehabilitation services. Additional participants will be recruited through posters and flyers distributed on social networks, at educational institutions, and through associations of autistic children’s parents. Children in Group B will be recruited from the family networks of Group A participants and matched for sex and age with their autistic peers. The target ratio between Groups A and B is approximately 1:2. During the development of the protocol, parents and professionals from recruitment sites provided valuable recommendations about the recruitment process, procedures and study goal.

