#### Microbiota analysis

3.6.1

Homogeneity of multivariate dispersions will be tested using the *betadisper* function in the *vegan* R package (54). Differences in microbial community composition (beta-diversity) between children with ASD and their NA peers will be determined using permutational multivariate analysis of variance (PERMANOVA) through the ADONIS2 function, also in *vegan*. Pairwise comparisons will be performed using the Wilcoxon rank sum test with Benjamini-Hochberg p-value adjustment (55).

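### The recruitment ratio for Groups A and B contradicts the stated group sizes, and a flat p < 0.05 covers some 44 to 54 outcomes without naming the sizing contrast as primary

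*Protocol article*

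**What the plan says.** **Group sizes.** Sections 2.2.1 to 2.2.3 give 100 children each for Groups A (autistic), B (no neurodevelopmental disorder) and C (other developmental disorders); Group A may go up to 150. Section 2.3, which mentions only Groups A and B, says "The target ratio between Groups A and B is approximately 1:2". The abstract's methods describe "200 age-/sex-matched NA peers (including 100 with developmental disorders other than autism", which is B plus C.

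**Sizing.** In section 2.2.4, "we used the formula for comparing two independent proportions in a two-sided hypothesis test". The inputs are "1.96 (corresponding to a 95% confidence level", "0.84 (corresponding to 80% power", 0.57 for Group A, and 0.37 described as "estimated malnutrition prevalence in NA children - Group B". The result is 94 per group, raised to 100. The same section then calls the prevalence of sensorimotor differences (SMD) a secondary comparison, with power close to 1.

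**Testing.** Section 3.6.2 states "Data will be considered statistically significant at a p-value < 0.05". The one adjustment is in section 3.6.1: "Pairwise comparisons will be performed using the Wilcoxon rank sum test with Benjamini-Hochberg p-value adjustment". That section compares autistic children with NA peers and does not say whether these are Group B, Group C or both.

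**Status of results.** No passage names a primary outcome or test. The introduction lists five aims side by side. Section 4.2 links the primary aims to the smartphone tool and also calls the aims hypothesis-generating. Section 3.6.2 attaches the exploratory label to the Kruskal–Wallis and clustering analyses.

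**The concern.** Two things are fixed badly in the text itself.

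First, the recruitment target contradicts the group definitions. Field staff working from section 2.3 would seek twice as many Group B children as sections 2.2.2 and 2.2.4 ask for.

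Second, the plan earns its 80% power for one comparison and then applies the same unadjusted threshold to dozens of others. If several diet, body-composition or startle measures cross 0.05 and malnutrition does not, nothing on the page says which result carries the conclusion. The undefined NA peers add to this. The 0.37 comes from general-population survey figures, while Group C is a clinical group, so A versus B and A versus C are different questions.

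**Working it through.** **1. The plan's own sample size** (inputs from section 2.2.4)

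n = (1.96 + 0.84)² × [0.57 × 0.43 + 0.37 × 0.63] / (0.57 − 0.37)²
= 7.84 × (0.2451 + 0.2331) / 0.04 = 93.7, so 94 per group.

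With 5% non-response: 94 / 0.95 = 98.9, so 99; the plan rounds to 100. The figure reproduces. With 100 per group, power for 57% versus 37% at two-sided 5% is 81%.

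**2. The ratio**

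| Source | Group A | Group B | Group C |
|---|---|---|---|
| 2.2.1–2.2.3, 2.2.4 | 100 | 100 | 100 |
| Abstract | 100 | 200 for B and C together, 100 of them in C | |
| 2.3, taken literally | 100 | about 200 | not mentioned |

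The first two rows agree: A:B:C = 1:1:1, and A:(B + C) = 100:200 = 1:2. Section 2.3 attaches the 1:2 to B alone. With Group A at its ceiling of 150, that reading would mean about 300 in Group B.

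**3. Number of outcomes** (my count from section 3.5; the document gives no total)

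| Domain | Low | High |
|---|---|---|
| Anthropometry and bioimpedance | 9 | 9 |
| Diet (high count adds the four example food groups) | 12 | 16 |
| Startle and prepulse inhibition | 8 | 10 |
| Startle habituation | 3 | 5 |
| General sensorimotor behaviour | 10 | 12 |
| Microbiota diversity | 2 | 2 |
| **Total** | **44** | **54** |

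This leaves out individual taxa. Without the two microbiota measures the range is 42 to 52.

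**4. False positives per contrast if no outcome differs**

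Expected number = k × 0.05: 2.2 for 44, 2.5 for 50, 2.7 for 54. This holds whatever the correlation between outcomes.

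Chance of at least one, if independent, = 1 − 0.95^k: 89.5% for 44, 92.3% for 50, 93.7% for 54.

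Many of these measures come from the same eyeblink traces, recalls or body scan, so independence is too strong. A simulation of 50 equally correlated two-sided tests (50,000 replicates, assumed correlations) gives about 81% at 0.3, 62% at 0.5 and 40% at 0.7.

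**5. What malnutrition means in the sizing contrast**

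The 0.37 in section 2.2.4 is 35% overweight or obese plus 2% extreme thinness. Section 3.5.3.1 gives thinness below −2 SD and severe thinness below −3 SD of BMI-for-age, and also undernutrition or malnutrition criteria by arm and neck circumference. The document does not say which of these defines the outcome behind the 0.37.

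**The case against.** The strongest reply is that the plan already has an implicit order. Section 2.2.4 sizes the study on malnutrition in A versus B and calls SMD prevalence secondary, so the lead contrast can be read off. Section 3.6.2 admits the large number of variables and labels some analyses exploratory, and section 4.2 calls the aims hypothesis-generating. Detailed multiplicity rules usually sit in an analysis plan, which is not shown. Much of this stands: a missing primary label would be no finding on its own. It does not remove the ratio conflict, which is on the page, or the threshold, which section 3.6.2 chooses to fix here without a family or order. The exploratory label is attached to the Kruskal–Wallis and clustering analyses and not to the mixed-effects models.

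A second reply is that family-wise error is the wrong yardstick for a study that uses Benjamini-Hochberg. When no outcome differs, however, the false discovery rate and the family-wise error rate are the same quantity, so the figures above do describe what that adjustment would address.

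Some stronger readings are tempting and are not supported:

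- *Only one contrast is powered.* The second power statement in section 2.2.4 is correct: 81.5% or 95% against 16.5% with 100 per group gives power of about 1.00. Malnutrition is the only contrast that sizes the study, which is a narrower statement.
- *The main test will pool B and C.* No passage says malnutrition will be tested on a pooled comparator, and section 4.1 describes three groups. Power for A = 100 against a pooled 200 would run from 91% if Group C's prevalence were 37% down to 37% if it were 57%. Those prevalences are assumptions, the document gives none for Group C, and the point does not rest on them.
- *Every listed outcome is tested unadjusted.* The microbiota pairwise comparisons are adjusted.

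**Conclusion.** The point holds in two parts. The A-to-B ratio in section 2.3 is wrong against sections 2.2.2 and 2.2.4; read literally it adds about 100 children to Group B. In addition, the flat 0.05 threshold covers roughly 44 to 54 listed outcomes while the one contrast that sizes the study has no stated primary status, no single outcome definition and, in section 3.6.1, no defined comparator.

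The expected 2.5 false positives per contrast depends on my count of about 50 and on no true effects. The 92% also needs independence, and the 40% to 81% range rests on assumed correlations. A reader might infer that the sample size is inadequate. It is not: with malnutrition A versus B as the single primary test at two-sided 5%, 100 per group is enough.

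**What to change.** 1. In section 2.3, state A:B:C = 1:1:1, and use 1:2 only for A against B and C combined.
2. Name malnutrition prevalence, Group A versus Group B, two-sided 5%, as the primary test. Give it one definition that is consistent with the 37% in section 2.2.4, reconciling extreme thinness there with the −2 SD and −3 SD cut-offs in section 3.5.3.1.
3. Fit group as three levels and report A–B and A–C separately. In section 3.6.1, say which group or groups the NA peers are.
4. Label the remaining outcomes secondary or exploratory, and extend the Benjamini-Hochberg adjustment of section 3.6.1 to the diet, body-composition and SMD domains.

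These are wording changes with no effect on the sample size. The cost is that fewer secondary results will reach significance. They should be settled before analysis begins, which section 2.1 schedules for the first trimester of 2026, while data are still being collected.

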**Analysis:**

Group comparisons will employ multivariate regression models, adjusting for age, sex, socioeconomic status and medication use. We hypothesize significant between-group differences in dietary patterns, nutritional status, microbiota profiles, and SMD measures. Objectively measured SMD in autistic children and adolescents is expected to correlate with symptom severity, dietary patterns, and differences in microbiota composition and diversity.

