### Study limitations

4.2

This study’s primary methodological limitation is its cross-sectional design, which inherently precludes the inference of causal relationships between exposures and outcomes. Our findings will thus be restricted to identifying non-causal associations that warrant future longitudinal or experimental validation. To enhance the robustness of our findings within this observational framework, we will employ multivariate regression models to control for key potential confounders (e.g., sex, age, socioeconomic status, use of medication). We will also conduct sensitivity analyses to assess the stability of these associations under different modelling assumptions.

The generalizability (external validity) of our findings will be constrained by the recruitment strategy. Sourcing participants from specialized private healthcare centers will likely yield a sample overrepresenting families of higher socioeconomic status and better healthcare access. This strategy may also bias the cohort toward more clinically severe ASD presentations, potentially underrepresenting children with milder phenotypes or those from marginalized communities who face barriers to diagnosis.

This sampling approach was chosen to safeguard internal validity and feasibility. Centralized recruitment was essential to secure a sufficient number of professionally diagnosed participants and to administer the study’s protocols consistently. Therefore, while the results will be most directly applicable to urban-dwelling autistic children within Ecuador’s private healthcare system, they will provide high-fidelity data on the hypothesized relationships under investigation.

This trade-off is justified for the hypothesis-generating aims of this study. Following Rothman’s principles, the initial test of a mechanistic pathway (e.g., between SMD and dietary patterns) requires a well-defined cohort where exposures and outcomes can be measured with precision, even at the expense of representativeness (71). The associations identified here will provide the foundational evidence necessary to design future longitudinal and population-representative studies.

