Self-medication represents an important limitation that our study will address. In Ecuador, self-medication, particularly with antibiotics, is common across various demographic groups (75). Excluding participants based on reported medication use would severely constrain recruitment. We will therefore account for this potential confounder by adjusting for medication use in multivariable statistical models when examining associations between gut microbiota composition and other outcomes. Specifically, medication use will be included as a covariate in linear models for alpha-diversity analyses and in PERMANOVA for beta-diversity comparisons. Finally, following previously used approaches (76), we will evaluate the robustness of our findings through sensitivity analyses that leverage the detailed medication data collected, exploring drug dosage, the specific reason for medication, and the prescribing source.

Another potential limitation of our study is that no formal cognitive ability assessment will be conducted. Cognitive level can influence dietary patterns independently of sensorimotor differences, for example, by affecting a child’s ability to express food preferences or aversions. Moreover, 30–40% of children with ASD also have co-occurring intellectual disability, a rate substantially higher than among NA peers (77). To address this potential confounding, we will use CARS scores as a proxy for phenotypic severity within the ASD group. Although CARS does not measure cognitive ability directly, it correlates with functional impairment and will allow us to explore whether associations differ by severity level. Nevertheless, residual confounding by unmeasured cognitive differences cannot be entirely ruled out.

The broad age range (3–17 years) of our sample represents another limitation, given the significant developmental heterogeneity within this period. While a narrower range would reduce variability, it would also compromise sample size and generalizability. To address this, age will be included as a covariate in all multivariate models to adjust for its potential confounding effects. Additionally, we have selected age-appropriate instruments to ensure that measurements are sensitive to developmental stages. Nevertheless, residual age-related variability may still influence our findings, and we acknowledge this trade-off.

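### Exploratory Kruskal–Wallis group comparisons cannot carry the age, sex, socioeconomic and medication adjustment that the protocol promises, and their p-values are not marked as descriptive

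*Protocol article*

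**What the plan says.** The abstract, under Analysis, commits to adjustment: "Group comparisons will employ multivariate regression models, adjusting for age, sex, socioeconomic status and medication use". Section 4.2 (Study limitations) repeats this twice: "we will employ multivariate regression models to control for key potential confounders (e.g., sex, age, socioeconomic status, use of medication", and "age will be included as a covariate in all multivariate models to adjust for its potential confounding effects".

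Section 3.6.2 sets the main method: "Statistical analysis will be performed using multilevel mixed-effects linear and nonlinear models in R Studio and Python". Among the advantages it claims for these models over standard parametric and non-parametric tests is that "they are more robust to violations of normality, which is common in biological data, and they do not require homoscedasticity". Later in the same paragraph, and after a single significance threshold of 0.05, comes the step at issue. It is introduced by "Given the large number of variables related to diet, nutritional status, ASD severity, and sensorimotor integration" and continues: "exploratory analyses will include the Kruskal–Wallis test to compare groups on non-normally distributed variables". No covariate-adjusted counterpart is named for that step.

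On balance by design, section 2.3 matches Group B to the autistic children on sex and age. Section 2.2.3, which defines Group C, states no matching. The abstract describes all 200 non-autistic peers, Group C included, as matched on age and sex. Nothing matches socioeconomic status or medication use.

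**The concern.** Diet and nutritional status belong to the study's first specific aim and sensorimotor measures to its third. For variables in these domains that are not normally distributed, the only group test named specifically is one that cannot hold a covariate. The age commitment in section 4.2 reaches multivariate models only, so it does not cover this test.

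Two things are at stake. First, over ages 3 to 17, any variable that changes with age carries that variation into the error of an unadjusted test, which costs power even when the groups have the same ages. Second, where groups differ on an unadjusted factor, that difference can pass as a diagnosis effect. This applies to socioeconomic status and medication use in every comparison, and to age in comparisons with Group C if the matching mentioned only in the abstract is not carried out.

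The section is also at odds with itself: it prefers mixed models because they cope with non-normality, then gives non-normality as the reason for a standard rank test.

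**Working it through.** **The plan's own figure.** Section 2.2.4 uses p1 = 0.57, p2 = 0.37, Z = 1.96 and 0.84:

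n = (1.96 + 0.84)² × [0.57 × 0.43 + 0.37 × 0.63] / (0.20)² = 7.84 × 0.4782 / 0.04 = 93.7, that is, 94. Allowing 5% non-response, 94 / 0.95 = 98.9, that is, 99, against the stated 100. The figure reproduces and this point does not touch it. It supplies the 100 per group used below.

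**Simulation.** From the document: three groups of 100, ages 3 to 17, alpha 0.05. Assumed, because the document gives no values: ages uniform over the range; a skewed (log-normal) outcome; age explaining 10% to 50% of its variance on the log scale; Group A shifted by 0.35 SD for power; Group C older on average by 0.5, 1 or 2 years for false positives. Each setting has 3,000 replicates. Kruskal–Wallis is compared with a linear model on the log outcome with age as covariate.

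*Power, ages balanced, Group A shifted 0.35 SD:*

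| Variance due to age | Kruskal–Wallis | Age-adjusted | Difference (points) |
|---|---|---|---|
| 0% | 0.700 | 0.724 | 2.4 |
| 10% | 0.689 | 0.755 | 6.5 |
| 30% | 0.700 | 0.860 | 16.0 |
| 50% | 0.671 | 0.952 | 28.1 |

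The 0% row shows that about 2 points come from ranks versus a correctly transformed model; the rest comes from adjustment. The pattern is as expected: adjustment shrinks the residual SD to √(1 − share), so 0.35 SD becomes 0.35/√0.9 = 0.37, 0.35/√0.7 = 0.42 and 0.35/√0.5 = 0.49 residual SDs.

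*Rejection rate with no true group effect:*

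| Mean age excess in Group C | Kruskal–Wallis (age share 10% / 30% / 50%) | Age-adjusted |
|---|---|---|
| 0 | 0.051 / 0.050 / 0.048 | 0.044–0.052 |
| 0.5 year | 0.059 / 0.073 / 0.083 | 0.039–0.051 |
| 1 year | 0.077 / 0.144 / 0.232 | 0.050–0.052 |
| 2 years | 0.187 / 0.483 / 0.732 | 0.046–0.055 |

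A check on scale: uniform ages over 14 years have SD 14/√12 = 4.04 years. A 2-year gap is 2/4.04 = 0.495 age SDs, and at a 50% share it moves the outcome by 0.495 × √0.5 = 0.35 SD. That is as large as the shift in the power table, and the rejection rate of 0.732 is of the same order as the power found there.

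**Where the age argument applies.** Raw intakes and bioimpedance measures are candidates. BMI-for-age and height-for-age z-scores are already standardised, and abdominal obesity is defined by percentiles for age and sex (section 3.5.3.1). Startle amplitudes are normalised and percent PPI is a within-child ratio (sections 3.5.4 and 3.5.4.1), so age dependence there is possible but not established by the document. The autism severity scale (CARS) is given to the autistic children only, so a comparison across the three groups does not arise for it.

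**The case against.** The strongest reply is that nothing is dropped. The mixed models are the stated analysis; Kruskal–Wallis comes afterwards, under an exploratory label, and no sentence makes it a substitute. A reader might infer that non-normal variables lose their adjusted comparison altogether; the text does not say so. A reader might also infer that a Shapiro–Wilk test on each raw variable decides the route, so that at n = 300 nearly every variable is diverted. The document applies Shapiro–Wilk to model residuals, as a diagnostic, and states no such gate. Both objections stand.

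On confounding, the abstract's matching covers Group C. With balanced ages the unadjusted test keeps its 5% level, so the false-positive figures need an age gap that the document does not predict. This stands too: the figures are conditional.

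On size, no single age share fits all the named variables, and for age-standardised z-scores the age argument falls away. That is why a range is given.

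Finally, a condensed article may leave the choice of model for each variable to a fuller plan. That excuses missing detail. It does not remove the tension between an adjustment promised for group comparisons and a named group test that cannot include it. Nor does the exploratory label settle the matter: section 4.2 calls the study's aims hypothesis-generating, section 3.6.2 gives one threshold, and nothing says which result governs if the unadjusted test and the adjusted model disagree.

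**Conclusion.** The point holds in a limited form. Section 3.6.2 adds an unadjusted group test for variables belonging to two of the study's aims, against the adjustment promised in the abstract and section 4.2 and against the section's own case for mixed models. Its p-values are not marked as descriptive.

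The cost in power is about 6 to 28 points with balanced ages, resting on an assumed 0.35 SD shift and an assumed age share of 10% to 50%. It concerns variables that depend on age, such as raw intakes and body composition, and possibly startle measures. False positives from age, 8–23% for a one-year gap and 19–73% for two years, arise only if Group C's ages differ from the others. Socioeconomic status and medication use are matched nowhere, so confounding by them does not depend on a failure of age matching; the document gives no figures from which to size it.

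The documents do not support the stronger conclusions that the adjusted analysis is abandoned or that most variables would be routed away from it. The point affects how these comparisons are read, not the sample size.

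**What to change.** In section 3.6.2, replace Kruskal–Wallis as an inferential test with a covariate-adjusted model that does not require a normally distributed outcome. Either proportional-odds (ordinal) regression, or the mixed or generalised linear models already planned, on a transformed outcome where needed, would serve. Include all four covariates listed in the abstract: age, sex, socioeconomic status and medication use. State that any Kruskal–Wallis result is descriptive only, and that a variable's marginal distribution does not decide whether its group comparison is adjusted.

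The cost is a sentence or two and standard software. The covariates are already being collected. The price is that the proportional-odds assumption, or the assumptions of the chosen model, must be checked.
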